##### Description for Intervention

Eligible participants will be randomly allocated in equal proportions between the two groups mentioned above to receive nerve block in the surgical preparation room. Each patient will receive 5 µg of sufentanil intravenously before nerve block. Participants will be placed in the lateral position, routinely disinfected and placed on the ultrasound probe using a sterile protective sleeve. All operations will be performed using a high-frequency line array probe on an M-Turbo ultrasound machine (SonoSite Inc., USA) and a short bevel puncture needle [Contiplex D continuous plexus block kit (B. Braun, Germany), 400 mm]. All patients will use 2 mL of 2% lidocaine for skin infiltration anaesthesia, explaining to the control group patients that this is nerve block puncture pain, and blinding the control group patients accordingly. Disinfect the skin and apply a towel, wrap the ultrasound probe in a sterile bag. Under ultrasound guidance, search for the erector spinae muscle, rhomboid muscle and trapezius muscle at the T4–T5 level, and insert the needle 3 cm next to the spinous process of the T5 thoracic vertebrae. Use in-plane needle insertion technology, and confirm under ultrasound that the end of the needle is located in the deep surface of the erector spinae muscle, and the puncture is successful. Based on previous literature and pre-experiments, we will select 0.5% ropivacaine 25 mL for the ESPB at the T4–T5 level and then use an indwelling catheter (depth 5 cm) and an electronic drug injection pump set at 0.2% ropivacaine 5 ml/h for continuous infusion [9]. All patients will be observed for 30 min after completion of the block, and the level of sensory block is measured and recorded every 5 min by another anaesthetist who is unaware of the group. Patients in group E who do not experience hypoalgesia during the observation period will be considered block failures and will be excluded at the time of final data unblinding. Patients in both groups will be given patient-controlled intravenous analgesia (PCIA) until 48 h after surgery. The PCIA protocol is as follows: sufentanil 100 µg + granisetron 6 mg + normal saline diluted to 100 ml, background dose 1.5 ml/h, self-controlled single dose 1.5 ml/time, locking time 30 min. If the static VAS score is ≥ 4, then parecoxib sodium 40 mg intravenous injection will be administered for rescue analgesia.

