### Interventions

#### Explanation for the choice of comparators {6b}

We describe all interventions as receiving continuous ESPB combined with general anaesthesia in full during the signing of the informed consent form. A sham nerve block is used for the comparator. In group C, only the erector spinae muscle is scanned with an ultrasound probe, followed by fixation of the line for the injection of the drug in the back and placement of the same electronic drug injection pump as in group E. In all patients, the electronic drug injection pump is wrapped in a black bag and kept for 48 h. The risks of ropivacaine infusion and systemic toxicity will be communicated to patients during the informed consent interview.

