##### Grouping

The groupings will be numbered sequentially and sealed in opaque envelopes by an independent person not involved in this study. Once participants are in the surgical preparation room, the appropriate serially numbered envelope will be opened by a trained operating room nurse not involved in the study to identify the grouping and the nerve block will be completed according to the grouping. Another researcher who is unaware of the grouping will measure the extent of the nerve block and record relevant data.

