### Criteria for discontinuing or modifying allocated interventions {11b}

Research interventions have been identified. Once an intervention is implemented, it cannot be modified.

The investigator will discontinue the participant if one of the following occurs during the course of the experiment:Participants request termination of the intervention during the course of the experiment.Attempt nerve block puncture operation ≥ 3 times.An unacceptable risk of a serious adverse event.For various reasons, post-operative follow-up cannot be completed.

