### Methods in analysis to handle protocol non-adherence and any statistical methods to handle missing data {20c}

This is an intention-to-treat study and we will explain the intervention in detail and emphasise matters of cooperation to patients during the pre-anaesthetic assessment and during obtaining informed consent, we suspect that few patients will offer non-compliance with the protocol. In the event of missing data, we will complete the data set by using multiple compensation methods as recommended by the statistical experts Hsu et al. [15] and will assess its effect by sensitivity analysis. We anticipate that few patients will be lost to follow-up due to the nature of clinical practice of the current trial intervention.

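### Excluding block failures from group E alone, after randomisation, contradicts the stated intention-to-treat analysis and can bias the comparison towards the block

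*Protocol article*

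**What the plan says.** The order of events is clear. Under *Grouping* in item {11a}, the envelope is opened in the preparation room "to identify the grouping and the nerve block will be completed according to the grouping". Block success or failure is therefore known only after randomisation.

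Under *Description for Intervention*, sensory testing covers both arms: "All patients will be observed for 30 min after completion of the block". The consequence falls on one arm: "Patients in group E who do not experience hypoalgesia during the observation period will be considered block failures and will be excluded". The same sentence sets the moment of exclusion at final unblinding.

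Item {6b} describes the comparator: "In group C, only the erector spinae muscle is scanned with an ultrasound probe". There is no block in group C that could fail.

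Item {20c} gives the analysis principle: "This is an intention-to-treat study". Missing data are to be completed by a multiple-imputation type of method and examined by sensitivity analysis. The article defines no per-protocol or modified intention-to-treat set, and nowhere confines the exclusion to a secondary analysis.

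Item {11b} lists reasons for discontinuing a participant. One is three or more tries at the block ("Attempt nerve block puncture operation"); another is follow-up that cannot be completed. It does not say whether these patients stay in the analysis.

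**The concern.** Objective {7} compares the two groups as allocated. Removing patients whose block did not take leaves group E selected for a working block, to be compared with unselected controls. Any trait that goes with block failure and also affects opioid use or pain is then thinned out in one arm only, and randomisation no longer protects the comparison.

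The contradiction has a second cost. Two incompatible rules stand for the primary result. If the choice between them is left until after unblinding, it can be influenced by the results.

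**Working it through.** **1. The plan's own figure.** Item {14} gives a 48-h dynamic VAS of 4.2 (SD 1.4) in controls and 3.6 (SD 1.1) with the block, with two-sided alpha 0.05 from item {20a} and 80% power.

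- Normal approximation: n = (1.4² + 1.1²) × (1.960 + 0.842)² / 0.6² = 3.17 × 7.85 / 0.36 = 69.1, so 70 per group.
- Noncentral t: power is 0.799 at n = 70 and 0.805 at n = 71, so 71.
- Dropout: 71 / 0.89 = 79.8, so 80.

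The stated 71 and 80 reproduce. The sizing arithmetic is not at issue here.

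**2. Overstatement if failed blocks behave like controls.** Let f be the share of group E without hypoalgesia. The document gives no value, so f is assumed at 5%, 10% and 20%. Successes are assumed to have mean 3.6 and SD 1.1, failures mean 4.2 and SD 1.4.

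- Difference with all patients as allocated: (1 − f) × 0.6.
- Difference after exclusion: 0.6, so the ratio is 1/(1 − f).
- Group E variance as allocated: (1 − f) × 1.1² + f × 1.4² + f(1 − f) × 0.6². At f = 10%: 1.089 + 0.196 + 0.032 = 1.317.

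Power is from the Welch noncentral t with 80 randomised per group and no other loss. The last column uses the normal approximation; its value at f = 0 is 70.

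| f | Failures among 80 | Difference, as allocated | Difference, failures excluded | Overstatement | Power, as allocated | Power, failures excluded | Evaluable per group for 80% power, as allocated |
|---|---|---|---|---|---|---|---|
| 5% | 4 | 0.57 | 0.60 | 5% | 0.805 | 0.843 | 78 |
| 10% | 8 | 0.54 | 0.60 | 11% | 0.755 | 0.835 | 89 |
| 20% | 16 | 0.48 | 0.60 | 25% | 0.641 | 0.816 | 116 |

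The relative overstatement depends only on f and on failures being control-like. The power columns also assume that 3.6 describes working blocks.

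**3. Type I error with no true effect.** Suppose failures would have done k SD worse than successes whatever the allocation. Dropping them moves the group E mean by k × f × SD. The SD is taken as 1.4, with 80 controls and 80(1 − f) remaining in group E.

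Example, f = 10% and k = 1: shift 0.14; standard error 1.4 × √(1/80 + 1/72) = 0.227; ratio 0.62; two-sided rejection probability 0.094.

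| f | k = 0 | k = 0.5 | k = 1 |
|---|---|---|---|
| 5% | 0.050 | 0.053 | 0.061 |
| 10% | 0.050 | 0.061 | 0.094 |
| 20% | 0.050 | 0.091 | 0.220 |

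**4. What cannot be computed.** The named primary outcome in item {12} is cumulative PCA consumption. The document gives no mean or SD for it, so the absolute bias on that outcome cannot be found. The calculation above uses the VAS because that is the sizing endpoint.

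**The case against.** Five points can be made for the plan.

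- **The rule is prespecified and the test is blinded and early.** Sensory level is recorded by an anaesthetist unaware of the group, within 30 minutes of the block and before surgery. A reader might infer from the timing at unblinding that patients could be picked on their results. The text does not support that: unblinding supplies the group label, and the sensory finding already exists. This limits manipulation. It does not cure the selection, because only one arm is filtered.
- **Bias is not certain.** This stands. With no true effect and failure unrelated to prognosis, type I error stays at 5%. The document offers no evidence that failures would have fared worse anyway.
- **Larger type I figures depend on a chosen reference.** Placing failures 1 SD above the arm mean gives about 32% at f = 20%, but that puts them 1.25 SD above the successes (1/0.8). The 22% above uses 1 SD from the successes. Either gap is an assumption.
- **Item {11b} is not a second exclusion from the analysis.** A reader might infer one, since three or more punctures can in practice occur only in group E. But the item speaks of discontinuing, which is compatible with intention to treat, and incomplete follow-up can arise in either arm and falls under the missing-data plan in {20c}. Item {11b} is ambiguous; it does not contradict {20c}.
- **A separate analysis plan might define the sets.** That would answer a silence. Here the article itself states two rules that conflict.

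**Conclusion.** The one-arm, post-randomisation exclusion and the intention-to-treat statement contradict each other, and nothing in the article reconciles them. Relative to the effect of the assigned strategy, the expected direction of bias is towards the block, but its size is unknown. Overstatement is 5% to 25% if 5% to 20% of blocks fail and failures behave like controls. Under no true effect, type I error ranges from 5% (failure not prognostic) to about 22% (20% failures, 1 SD worse than successes). At a 5% failure rate it is at most about 6.1% in the cases examined. Both the failure rates and the prognostic gaps are assumptions. It is therefore right to say that control of type I error is not guaranteed, and too strong to say that it is lost. The contradiction still has to be resolved, because it leaves the population for the primary result undefined and one reading gives up the protection of randomisation.

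**What to change.** Make these changes before unblinding:

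- In *Description for Intervention*, delete the exclusion of block failures from the primary analysis.
- In {20c}, state that all randomised patients are analysed in their allocated group for the primary outcome and the efficacy secondary outcomes.
- In {11b}, state that patients who meet a listed criterion stay in the analysis unless they withdraw consent for use of their data, with missing outcomes handled under {20c}.
- Report block failures and repeated puncture attempts by count.
- Show the analysis without block failures only as a labelled sensitivity analysis.
- Plasma ropivacaine and post-puncture reactions may be reported by treatment received.

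The administrative cost is a short amendment through the ethics committee under {25}; no new data are needed. The statistical cost should be acknowledged: the estimate may be less favourable. On the sizing endpoint and the assumptions above, power with 80 per group and no other loss would be about 0.81, 0.76 and 0.64 at failure rates of 5%, 10% and 20%. The article does not say whether its 11% allowance was meant to cover block failures. The team should state the failure rate it expects and either accept the resulting power or revisit the sample size.

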##### Introduction for investigators

The study will be done with the joint participation of the Anaesthesia Department, the Breast Surgery Department, the Central Laboratory and the Operating Theatre Nursing Department. The Anaesthesia Department participants in the study have extensive experience in nerve blocks and have received specific training in ultrasound-guided ESPB.

### Criteria for discontinuing or modifying allocated interventions {11b}

Research interventions have been identified. Once an intervention is implemented, it cannot be modified.

The investigator will discontinue the participant if one of the following occurs during the course of the experiment:Participants request termination of the intervention during the course of the experiment.Attempt nerve block puncture operation ≥ 3 times.An unacceptable risk of a serious adverse event.For various reasons, post-operative follow-up cannot be completed.

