**Methods:**

In this prospective, randomised, controlled trial, we will recruit 160 patients, aged 18–80 years, scheduled for elective MRM surgery under general anaesthesia. They will be randomly assigned to two groups: a continuous ESPB group (group E) and a sham block group (group C). Both groups of patients will have a nerve block (group C pretended to puncture) and an indwelling catheter fixed prior to surgery. Electronic pumps containing LA are shielded. The primary outcome is the total consumption of analgesic agents. The secondary outcomes include the levels of inflammation-related cytokines; the occurrence of chronic pain (post-mastectomy pain syndrome, PMPS); static and dynamic pain scores at 2, 6, 12, 24 and 48 h postoperatively; and post-operative and post-puncture adverse reactions.

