### Outcomes {12}

#### Primary outcome

The primary outcome is the cumulative PCA consumption, including the sum of background dose and self-control dose.

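### The discontinuation rule in section {11b} acts on the participant, not the block or infusion; taken literally it removes randomised patients from an intention-to-treat trial, and one trigger exists only in group E

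*Protocol article*

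**What the plan says.** Section {11b} of the protocol article, on discontinuing or modifying allocated interventions, says: "The investigator will discontinue the participant if one of the following occurs during the course of the experiment". Four events follow. The first is "Participants request termination of the intervention during the course of the experiment". The second is three or more attempts at the nerve block puncture, and the third is an unacceptable risk of a serious adverse event. The fourth is "For various reasons, post-operative follow-up cannot be completed".

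Section {20c} declares the trial intention-to-treat and plans imputation with a sensitivity analysis for missing data. Section {18b} gives participants the right to withdraw from the study and has the reasons recorded.

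On the control procedure, the Abstract (Methods) describes the block step as "group C pretended to puncture", and section {6b} says "In group C, only the erector spinae muscle is scanned with an ultrasound probe".

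On the outcome, the article says "The primary outcome is the cumulative PCA consumption, including the sum of background dose and self-control dose". The subsection describing the intervention says "Patients in both groups will be given patient-controlled intravenous analgesia (PCIA) until 48 h after surgery".

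**The concern.** Stopping a treatment and leaving a trial are different events. Under intention-to-treat, a patient whose block is abandoned or whose infusion stops early still contributes outcome data in the assigned group. Section {11b} does not keep the two apart. It acts on the participant, and it gives three treatment events the same consequence as being unable to complete follow-up.

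Site staff who follow the sentence literally would stop observing randomised patients for reasons arising from treatment. Patient-controlled analgesia (PCA) consumption, pain scores and post-mastectomy pain syndrome (PMPS) data that could have been collected would then have to be imputed. Because the puncture trigger belongs to one arm, patients who are hard to block could be lost from group E while comparable patients remain in group C.

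**Working it through.** **1. When the triggers act.** The subsection on grouping and section {16c} have the envelope opened in the surgical preparation room, before the block. The puncture trigger, and any event after the block begins, therefore falls after randomisation.

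**2. Which arm each trigger can reach.**

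| Trigger in {11b} | Group E | Group C |
|---|---|---|
| Request to end the intervention | yes | yes |
| Three or more block punctures | yes | no: scanned only, puncture pretended |
| Unacceptable serious-event risk | yes | yes |
| Follow-up cannot be completed | yes | yes |

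Group C does receive lidocaine skin infiltration, but that is not an attempt at the nerve block puncture.

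**3. Whether other sections settle the meaning.**
- {18a} sets assessments to 48 h and at 3, 6 and 12 months, without mentioning discontinued patients.
- {18b} covers withdrawal by the participant.
- {22} follows adverse events to recovery and says nothing either way about outcome follow-up.
- {20c} covers non-adherence and missing data, but does not say that discontinued patients stay under observation.

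**4. Whether the data remain observable.** Intravenous PCA is delivered separately from the ropivacaine pump, with "background dose 1.5 ml/h, self-controlled single dose 1.5 ml/time, locking time 30 min". The background alone is 1.5 ml/h × 48 h = 72 ml. At 100 µg in 100 ml (1 µg/ml) that is 72 µg, whether or not the block was completed. The primary outcome, the pain scores and the later contacts can all still be recorded.

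**5. Reproducing the sample size in {14}.** Inputs: 48 h dynamic VAS 4.2 (SD 1.4) against 3.6 (SD 1.1), difference 0.6, two-sided 0.05, power 80%.
- Pooled SD = √((1.4² + 1.1²)/2) = √1.585 = 1.259.
- Normal approximation: n = 2 × 1.585 × (1.960 + 0.842)² / 0.6² = 69.1, so 70 per group.
- Unequal-variance t-test: power 79.9% at 70 and 80.5% at 71, so 71 per group, as stated.
- Dropout: 71 / 0.89 = 79.8, so 80 per group, as stated.

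**6. Effect on power if only group E loses patients.** The loss fractions are assumptions, since the article gives none. The standard error is √(1.4²/80 + 1.1²/nE), and power comes from the noncentral t distribution.

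| Assumed loss in E | nE | Standard error | 0.6 / SE | Power |
|---|---|---|---|---|
| 0% | 80 | 0.199 | 3.01 | 85.0% |
| 2% | 78 | 0.200 | 3.00 | 84.6% |
| 5% | 76 | 0.201 | 2.98 | 84.3% |
| 10% | 72 | 0.203 | 2.95 | 83.5% |
| 15% | 68 | 0.206 | 2.92 | 82.6% |

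These figures apply to the VAS used for planning, not to PCA consumption, for which the article gives no planning mean or SD.

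**7. Selection.** If k of n patients in an arm are lost, and they differ from those retained by a gap d, the retained mean differs from the full mean by (k/n) × d. The article gives neither k by arm nor d, so no value can be put on this.

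**The case against.** The strongest reply is that {11b} concerns treatment only. Its heading names interventions, its opening sentences are about the intervention, its first trigger is a request to end the intervention, and {18b} uses different words for leaving the study. This stands as a possible reading. It fits poorly with a rule whose object is the participant, and with a fourth item about follow-up. The text leaves the question open, and staff should not have to guess.

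A second reply is that a journal article may leave continued follow-up to the full protocol. That would answer a complaint about silence. Here a rule is stated, and its wording is the defect.

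A third reply is that the one-arm trigger is a sensible safety limit and should be rare with experienced operators trained in the block. That is probably right, and it limits the practical effect. Some of these patients may also overlap with the block failures covered by the separate exclusion in the description of the intervention.

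Two stronger conclusions are tempting:
- A reader might infer that {11b} excludes patients from analysis. It does not say so. The explicit analysis exclusion is that block-failure rule, which is a different matter and is not counted here.
- A reader might infer a bias of known size or direction. Suppose all 9 patients in one arm's dropout allowance (80 − 71) were lost, each 1 SD above the arm mean. The VAS difference would be 4.2 − (288 − 9 × 4.7)/71 = 0.739 if they came from E, and (336 − 9 × 5.6)/71 − 3.6 = 0.423 if they came from C, against 0.6. The shifts reverse if they were 1 SD below. Neither the counts nor the 1 SD gap has a source in the article, and the allowance also covers ordinary dropout. No bias range is claimed.

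**Conclusion.** The point holds as a defect of wording with a real consequence if the text is followed. Section {11b} permits, and taken literally requires, removing randomised patients from the trial for treatment events, contrary to {20c}. Because the puncture trigger exists only in group E, any such loss could be unequal between arms.

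Its size cannot be stated. Trigger rates are absent and probably low, the cost in power is small under the assumed losses, and the size and direction of any bias are unknown. The conclusion rests on the wording of {11b} and on group C receiving no block puncture. It does not rest on any assumed rate.

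**What to change.** Reword {11b} so that a request to stop, three or more puncture attempts, or unacceptable serious-event risk ends the block or infusion only and is not withdrawal from the trial. Then state that:
- such patients stay in PCA and VAS recording to 48 h and in the 3, 6 and 12 month follow-up, unless they withdraw consent to follow-up under {18b};
- they are analysed as randomised;
- the stop time and reason are recorded on the case record form in both arms;
- inability to complete follow-up is taken out of this list and handled as missing data under {20c}.

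The cost is a few sentences and a short case record form entry, using contacts already scheduled. The downside is that off-treatment data may dilute the estimated effect of a fully delivered infusion, which the stated intention-to-treat principle already accepts.
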